### Statistical methods

The estimation of effect size for selected variables will be the calculation of two-sided 95% confidence intervals.

Primary endpoint one will be set due to the clear duration difference between colorectal surgery and the other types of surgery (laparoscopic cholecystectomy and laparoscopic hernia repair) a normal distribution of the data can be excluded. Therefore, a nonparametric test, namely the exact Mann–Whitney *U*-test will be used (type I error = 2.5% one-sided).

Primary endpoint two (only if H0_PE1_ is rejected), will be set by checking data sets for normal distribution (test of normality: Kolmogorov-Smirnov with Lilliefors significance correction, type I error = 5%). In the case of normal distribution the *t*-test for independent samples with correction for heteroscedasticity (Levene’s test, type I error = 5%) will be applied. In the case of a significant deviation from the normal distribution the exact Mann–Whitney *U* test will be used instead. In both cases the type I error will be 2.5% one sided.

Metric variables data sets will be checked for normal distribution (test of normality: Kolmogorov-Smirnov with Lilliefors significance correction, type I error = 5%). Normally distributed data sets will be compared between the groups by the *t*-test for independent samples with correction for heteroscedasticity (Levene’s test, type I error = 5%). If there is a significant deviation from the normal distribution the exact Mann–Whitney *U* test will be used instead.

Ordinal variables will be checked by the exact Mann–Whitney *U* test and nominal variables by the exact chi-square homogeneity test or, for 2 × 2 frequency tables the Fisher's exact test.

All tests will be two-sided with a confidence level of 95% (*P* <0.05). As no adjustment of the *P* values will be made, the resulting *P* values will only be descriptive.

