## Methods/Design

### Objectives and hypotheses

The primary objective of the present randomized trial is to investigate the mean operative time and to study the frequency and intensity of postoperative shoulder pain in patients undergoing laparoscopic cholecystectomy, colorectal surgery, and hernia repair with AirSeal™ (group A) compared with a standard pressure CO_2_ insufflator (group S).

The first primary endpoint will be whether the time of surgery in group A is more than or equal to the time of surgery in group S (H0_PE1_) or whether the time of surgery in group A is less than the time of surgery in group S (H1_PE1_).

The second primary endpoint will be whether shoulder pain in group A is more than or equal to shoulder pain in group S (H0_PE2_) or whether shoulder pain in group A is less than shoulder pain in group S (H1_PE2_).

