### Study design and randomization

After screening for eligibility is performed and informed consent is obtained, patients will be randomly stratified regarding type of operation in a 1:1 ratio into one of the following study arms: laparoscopic surgery with an AirSeal™ CO_2_ pressure insufflator (Surgiquest Inc., Milford, USA) (group A, experimental arm) or laparoscopic surgery with a standard CO_2_ pressure insufflator (Olympus America Inc. UHI-3, Center Valley, PA, US) (group S, control arm).

Patients are randomized using a web-based, central randomization and registration system. Treatment according to randomization (operation with AirSeal™ or standard CO_2_ pressure pneumoperitoneum) must be carried out within 14 days after randomization. For the study flow of the trial according to CONSORT guidelines, please see Additional file 1.

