### Statistical considerations

From a statistical point of view the present trial shows a confirmatory status, superiority approach and a parallel group design (group A with AirSeal™ use versus group S with standard CO_2_ pressure pneumoperitoneum insufflator use). The type I error preservation by the gatekeeping approach (primary endpoint one: time of surgery (in minutes) and primary endpoint two: shoulder pain at 48 hours after end of surgery (measured using VAS)) was calculated. Stratification according to the type of surgery was done.

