### Sample size estimation

On the basis of a comparison of two proportions, a sample size of 182 (n = 91 per group) is needed to have 80% power at a 5% significance level, assuming a dropout rate of 5%.

Data, assumptions and conditions are: type I error (2.5% one-sided), type II error (20%), non-parametric test (Mann–Whitney *U*-test), n (group A): n (group S) (ratio of 1:1) and per-protocol analysis:

(1)$$\begin{array}{l} \mathrm{group}\;A\;\left(\mathrm{mean}\;\pm \;\mathrm{standard}\;\mathrm{deviation}\right):\;74,8\;\pm \;41,3\;\min\\ \mathrm{group}\;S\;\left(\mathrm{mean}\;\pm \;\mathrm{standard}\;\mathrm{deviation}\right):\;93,5\;\pm \;41,3\;\min \end{array}\;\}\Delta =20\%$$

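### Operation time is tested without the strata used in randomisation, so the gatekeeper test has less power than a stratified test and may be conservative

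*Protocol article*

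**What the plan says.** Under Study design and randomization, the article states that "patients will be randomly stratified regarding type of operation in a 1:1 ratio". Statistical considerations repeats it: "Stratification according to the type of surgery was done". Statistical methods then fixes the test for operation time: "namely the exact Mann–Whitney *U*-test will be used (type I error = 2.5% one-sided". No stratum term appears. The reason given for a rank test is that normality can be excluded "due to the clear duration difference between colorectal surgery and the other types of surgery".

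Shoulder pain is tested formally only if the null hypothesis for operation time is rejected. Its test is an independent-samples t-test or, after a normality pre-test, a Mann–Whitney test, again without strata: "In the case of a significant deviation from the normal distribution the exact Mann–Whitney *U* test will be used instead". The sample size section plans on the same basis ("type I error (2.5% one-sided), type II error (20%), non-parametric test"), with a single standard deviation of 41.3 min for all procedures together.

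The test is named in the article, so this is not a detail left open for an analysis plan.

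**The concern.** The article names a factor that strongly predicts operation time and stratifies the randomisation on it. It then uses that factor only to argue against normality. A rank test copes with a non-normal shape, but it does not remove the difference between procedures. Pooling ranks short procedures against colorectal resections, and the spread between them goes into the reference variance of the test.

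Two things follow. The pooled test has less power than one that compares patients within type of operation. And if the randomisation balances the arms within strata, the reference variance is larger than the true variance of the statistic, so the test rejects less often than 2.5% under the null. Since operation time is the gatekeeper, power lost there also lowers the chance that shoulder pain is ever formally tested.

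**Working it through.** **1. The plan's own figure.** Inputs from Sample size estimation: means 74.8 and 93.5 min, SD 41.3 min, 2.5% one-sided, 80% power, 5% dropout. The difference is 93.5 − 74.8 = 18.7 min, which is 20% of 93.5.

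n per arm = 2 × (1.960 + 0.842)² × 41.3² / 18.7² ≈ 76.6, so 77; the exact t version gives 78. The usual 10% addition for a rank test gives 78 × 1.1 = 85.8, so 86. Dropout gives 86 / 0.95 = 90.5, so 91. The stated 91 per group is reproduced, with 86 per group evaluable. Strata play no part in it.

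**2. Size of the pooled test when arms are balanced within strata.** Let r be the share of rank variance that lies between types of operation. Balance removes that share from the true variance of the statistic, but the pooled test still counts it. The true one-sided size is then about 1 − Φ(1.96 / √(1 − r)):

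| r | True size |
|---|---|
| 0.1 | 1.9% |
| 0.2 | 1.4% |
| 0.3 | 0.96% |
| 0.5 | 0.28% |

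**3. Simulation.** The article gives no case mix, no durations by procedure and no block size, so these are assumptions: 172 evaluable patients, overall mean 93.5 and SD 41.3 min, log-normal times within strata, cholecystectomy and hernia repair of equal duration, and blocks of 4 within each of three strata. Effects are proportional reductions. Each cell shows the pooled Mann–Whitney test, then van Elteren.

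| Colorectal share, extra duration | r (ranks) | Size | Power, 10% reduction | Power, 20% reduction |
|---|---|---|---|---|
| 10%, 60 min | 0.12 | 1.9% / 2.5% | 37% / 42% | 95.3% / 96.2% |
| 20%, 60 min | 0.27 | 1.0% / 2.4% | 38% / 50% | 96.5% / 98.6% |
| 20%, 80 min | 0.43 | 0.4% / 2.4% | 47% / 73% | not tabulated |
| 33%, 60 min | 0.47 | 0.4% / 2.5% | 31% / 61% | 97.5% / 99.7% |

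With 10% colorectal and a gap of 40 to 60 min, the pooled size is about 1.9–2.1%. More extreme mixes (50% and 60 min; 33% and 75 min) bring it to 0.1% or less. The formula in step 2 agrees: r = 0.27 gives 1.1% and r = 0.47 gives 0.36%.

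A second set of runs, with the same arm size, mean and SD but other assumed case mixes, gave a pooled size of 0.4–1.7% against 2.2–2.5%. Power at a 10% reduction was 34–42% pooled against 40–70% stratified.

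**4. Dependence on blocking.** On allocation, the article says only: "Patients are randomized using a web-based, central randomization and registration system". With 20% colorectal and an 80 min gap, the pooled size is 0.6% with blocks of 6 and 0.5% with blocks of 10. With unblocked allocation within strata it returns to nominal (2.6% simulated). The power gap remains without blocking: 36–45% pooled against 40–69% stratified at a 10% reduction in the second set of runs.

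**5. Power at the planned effect.** Suppose the pooled test would have exactly 80% power if strata explained nothing. Under balance its power is Φ(0.842 / √(1 − r)), which is 84% at r = 0.3 and 91% at r = 0.6. For a stratified test it is Φ(2.802 / √(1 − r) − 1.96), which is 92% and 99%. The simulated values at 20% are higher because a proportional reduction in skewed times is easier for a rank test to detect. Absolute powers therefore depend on the assumed shape, and the comparison between the two tests is what carries weight.

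**The case against.** The strongest reply is that nothing promised by the plan is lost. The type I error is protected, the design effect is a 20% reduction, and there the pooled test reaches its 80%. This stands. The gatekeeper argument has little force at the planned effect and applies to smaller ones.

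A reader might infer that the test is far more conservative than 2.5% as a matter of fact. The documents do not support that. They call the duration difference clear but give it no size, and they state neither the colorectal share nor any blocking. The primary efficacy set is per protocol and drops conversions to open surgery, so exact balance within strata is not guaranteed there either. The possible range runs from almost nominal to very conservative.

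A reader might also extend the point to shoulder pain. Nothing in the article says that type of operation predicts shoulder pain, and no harm from the normality pre-test has been shown.

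Finally, a reader might object that a rank test yields no estimate of time saved, although "The primary objective of the present randomized trial is to investigate the mean operative time". That goes too far: the article plans 95% confidence intervals for selected variables and reports arithmetic means. It does not say that any such estimate will be adjusted for type of operation.

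What the reply does not remove is that the stratified test had the higher power in every scenario, blocked or not.

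**Conclusion.** The point holds as a matter of efficiency, not of validity. The operation-time test omits a stratification factor that the article itself describes as clearly related to operation time.

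- **Power:** at a 10% reduction the pooled test is about 5 to 30 percentage points below van Elteren in the tabulated scenarios (42 − 37 and 61 − 31). Across the second set of case mixes the ranges are 34–42% against 40–70%. At the planned 20% reduction both tests exceed 80%.
- **Size:** with balance within strata, the true one-sided size is from about 2% to below 0.5% in most scenarios examined. With unblocked allocation it stays near 2.5%.

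These figures rest on assumed case mixes, duration gaps, log-normal times and 86 evaluable patients per arm. The direction of the power difference was the same in every scenario, but its size cannot be fixed from the article. No gain is shown for shoulder pain.

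**What to change.** In Statistical methods, replace the pooled Mann–Whitney test for operation time with a van Elteren (stratified Wilcoxon) test by type of operation, one-sided at 2.5%. Beside it, report a stratum-adjusted effect estimate with a 95% confidence interval. A difference in mean minutes adjusted for type of operation would match the stated objective; a ratio from a model of log time would match the relative effect used for planning. State whether allocation is blocked within strata.

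Stratifying the shoulder-pain test in the same way is optional, for consistency with the randomisation.

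The change needs no further patients or data, since type of operation is known for everyone randomised. It does alter a confirmatory test while recruitment is under way, so under the article's own rule it is an amendment requiring ethics committee approval. It should be settled before any unblinded analysis.

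### Operating time is framed in mean minutes, but its gatekeeping test is a Mann–Whitney test that ignores operation type, so a saving confined to colorectal cases would largely be missed

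*Protocol article*

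**What the plan says.** All references are to the protocol article.

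- **Objectives and hypotheses.** The objective is introduced in terms of the mean: "The primary objective of the present randomized trial is to investigate the mean operative time". The formal alternative names no summary measure; it asks only "whether the time of surgery in group A is less than the time of surgery in group S".
- **Sample size estimation.** The inputs are means and SDs: 74.8 ± 41.3 min for AirSeal, 93.5 ± 41.3 min for standard, a 20% difference. The conditions read "type I error (2.5% one-sided), type II error (20%), non-parametric test", so the rank test is already named here.
- **Study design and randomization** and **Statistical considerations.** Allocation is stratified by type of operation.
- **Statistical methods.** Normality is ruled out because colorectal operations last clearly longer than the other two types. "Therefore, a nonparametric test, namely the exact Mann–Whitney" U-test then follows, at one-sided 2.5%. No stratified or adjusted form is stated. Shoulder pain is tested only if this test rejects.
- **Presentation of the results.** Metric variables are described by arm, including the arithmetic mean and SD.

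**The concern.** A Mann–Whitney test addresses the chance that an AirSeal operation is shorter than a standard one. That agrees with a comparison of means under a common shift, but need not when the effect differs by operation type. Two things go wrong in a mixture of short and long procedures.

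1. **Type is ignored.** Stratified allocation balances the types between arms, but the unstratified test still counts the large between-type spread as noise. It becomes conservative and loses power.
2. **Ranks discount minutes saved in long cases.** A colorectal operation made 30–50 min shorter still ranks above nearly all gallbladder and hernia cases, so the saving hardly moves the statistic.

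The Discussion ties harm to time under pneumoperitoneum, so minutes saved in the longest operations matter to the trial's own rationale. Because this test is the gate, a missed saving also blocks the confirmatory test of shoulder pain.

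**Working it through.** **1. The plan's own figures.** 93.5 × 0.80 = 74.8, so the 20% is a difference in means of 18.7 min; d = 18.7/41.3 = 0.453. For a comparison of means, n = 2(1.96 + 0.8416)²/0.453² ≈ 77 per group (77.5 with the t distribution). Dividing by the relative efficiency 3/π gives 82 for Mann–Whitney, and 82/0.95 gives 87 per group, 174 in total. The article states "a sample size of 182 (n = 91 per group) is needed". That total is not reproduced exactly, but it exceeds 174, and 86 evaluable per arm (91 × 0.95) gives about 82% power under a normal shift. The total is therefore not shown to be too small. This calculation assumes a common shift and does not represent the mixture.

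**2. Assumed mixes.** The article gives no case shares or times by type. Three mixes (gamma times) were set to match the planning mean and approximate SD. With p the colorectal share, m₁, s₁ the mean and SD of short operations and m₂, s₂ those of colorectal:

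mean = (1−p)m₁ + p·m₂; SD = √[(1−p)s₁² + p·s₂² + p(1−p)(m₂−m₁)²]

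| p | Short: mean (SD) | Colorectal: mean (SD) | Overall mean | Overall SD | Mean saving if colorectal only, 30% |
|---|---|---|---|---|---|
| 28% | 70 (14) | 153.9 (23) | 93.5 | 41.3 | 0.28 × 0.30 × 153.9 = 12.9 min |
| 20% | 75 (22) | 167.5 (40) | 93.5 | 45.6 | 0.20 × 0.30 × 167.5 = 10.1 min |
| 35% | 65 (15) | 146.4 (30) | 93.5 | 44.4 | 0.35 × 0.30 × 146.4 = 15.4 min |

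**3. Rejection rates**, 86 per arm, one-sided 2.5%, range over the three mixes:

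| Scenario | Planned Mann–Whitney | Rank test stratified by type | Type-adjusted means |
|---|---|---|---|
| No effect | 0.5% or less | – | 2.0–2.6% |
| Uniform 20% saving | ≥96% | ≥96% | ≥96% |
| Uniform 10% saving | 28–56% | 65–95% | 67–96% |
| Colorectal only, 30% | 5–18% | 33–90% | 72–100% |
| Short operations only, 20% | 84–100% | 97–100% | 76–99% |

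**4. Splitting the colorectal-only gap.** In the order of the mixes above, stratifying the rank test alone gives about 82%, 33% and 89%; adjusted means give about 100%, 74% and 100%. Moving instead from ranks to an unadjusted Welch comparison of means, still ignoring type, gives 34–94%. Both causes contribute. With a uniform 10% saving the gap is almost wholly stratification.

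**5. A second set of assumptions** (two-stratum lognormal times, within-type CV 30%). The null rate of the planned test is 0.4–0.7%, against 2.4–2.5% for adjusted means. For a 35% saving in colorectal cases only:

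- 30% colorectal (75 and 137 min; mean falls from 93.6 to 79.2): Mann–Whitney 52%, Welch 87%, adjusted means 93%.
- 20% colorectal (78 and 155.5 min; 93.5 to 82.6): 15%, 51% and 70%.

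**6. Opposite effects by type.** With 28% colorectal, short operations 10 min faster and colorectal 35 min slower, the mean changes by −0.72 × 10 + 0.28 × 35 = +2.6 min; with 12 and 45 min it changes by −8.64 + 12.6 = +4.0 min. The planned test declares AirSeal faster in 30–53% of such trials, adjusted means in at most 0.2%. With 35% colorectal and larger slowdowns the planned test does so in only 2–3%. In the lognormal set it is 36–86% at 20–30% colorectal and about 1–2% at 40% (short operations −20%, colorectal +30%).

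**The case against.** **The hypotheses do not name a mean, and the planned and analysed tests agree.** Both are true, and means and SDs are routine inputs to a Mann–Whitney sample size. But the sentence that introduces the hypotheses speaks of the mean, and the planned effect is a mean difference. Prespecifying a test does not make it answer that objective, and neither point excuses leaving out the stratification factor.

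**Nothing is lost under the planned effect.** Correct. If both types gain, but colorectal more (15% and 25%), the planned test still has 85–99% power; at 10% and 30% it has 59–89%. The severe loss needs a benefit concentrated in colorectal cases.

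**Means are not always better.** Also correct: when only short operations are shortened, the rank tests do as well as or better than adjusted means.

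Three stronger readings are tempting and not supported:

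- A reader might infer that the trial is likely to declare AirSeal faster when its mean time is longer. That needs opposite effects by operation type, which nothing in the article suggests, and it depends heavily on the mix.
- A reader might infer that the result could not be set against the planned 20%. It can, because the arm means will be reported.
- A reader might fault the promise of intervals for selected variables ("The estimation of effect size for selected variables will be the calculation of two-sided 95% confidence intervals"). Which variables are meant is commonly left to the full protocol or analysis plan, so this is no defect.

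**Conclusion.** The point holds as a mismatch between the stated objective and the gate test, made worse by a test that ignores the stratification factor. The planned test's true level is under 1% in every mix in the tables above. Its power for a 30% colorectal-only saving (about 10–15 min on the overall mean) is about 5–18%, against 33–90% for a stratified rank test and 72–100% for adjusted means. The ranks alone do not explain the whole gap.

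The percentages are illustrative: they rest on assumed shares, times and spreads by type. The direction of the colorectal-only result was the same in every mix and under both distributions. A rejection with a longer AirSeal mean is possible but hypothetical. The article's stated reason for using ranks does not compel them, since a type-adjusted comparison of means held its level at about 86 per arm. No inflation of type I error and no shortage of patients follows from this point. It should be corrected, but it does not invalidate the design.

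**What to change.** In Statistical methods, define the primary analysis of operation time as the difference in mean minutes (AirSeal minus standard), adjusted for or standardised over the three operation types. Use a linear model with robust standard errors, or a permutation test of that difference within type, at one-sided 2.5%. Report its two-sided 95% confidence interval. Keep a rank test stratified by operation type as a sensitivity analysis.

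If a rank test stays as the gate, stratify it by operation type, reword the objective to match, and report the type-adjusted mean difference with its interval as the effect estimate.

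**Cost.** No extra patients, a short text change and a few lines of code. Very long operations weigh more in a mean, and power is lower than with ranks if only short operations are shortened. The change must be made and dated before anyone sees operation times by arm. That needs care here: times are routinely documented, the described blinding covers only the pain assessment, and Trial status expected recruitment to end by March 2014.

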### Secondary endpoints

Blood sample remains will be collected during routinely preformed venepuncture prior to surgery, intraoperatively after pneumoperitoneum skin incision, after skin suture and 24 hours postoperatively. They will be kept and used for immunological evaluation. All routine laboratory diagnostics will be performed immediately after blood collection. For the determination of the target parameters the EDTA (Ethylenediaminetetraacetic acid) plasma must be frozen by -80°C. All interleukins and cytokines will be measured at the end of patient recruitment in one sequence. Blood gas analysis and documentation of the ventilation volume will be performed. This intraoperative data will be also collected by the survey. Analgetic requirements, wound infections, anastomotic leakage and postoperative hemorrhage of all the patients in the postoperative period and length of hospital stay will be also recorded.

The immunological aspects will be: changes in the concentration of certain cytokines and angiogenic factors serum levels in the early postoperative period, and target parameters (soluble interleukin-1 receptor family member ST2 (sST2), interleukin (IL)-6, IL-8, IL-10, vascular endothelial growth factor A (VEGF-A) and endostatin).

The anesthesiological aspects will be: tidal volume, positive end expiratory pressure (PEEP), peak pressure, respiratory minute volume, acid–base balance and CO_2_ elimination in the patients, measured before insufflation, during surgery and after deflation of the pneumoperitoneum.

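### Secondary biomarker and anaesthesiological comparisons make no adjustment for operation type and no stated use of the baseline value, and a normality pre-test picks the test: a loss of precision, not of validity

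*Protocol article*

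**What the plan says.** The Secondary endpoints section describes the immunological outcome as "changes in the concentration of certain cytokines and angiogenic factors serum levels in the early postoperative period", covering six named biomarkers. Blood is drawn "prior to surgery, intraoperatively after pneumoperitoneum skin incision, after skin suture and 24 hours postoperatively", so the first of four samples is a pre-intervention value. The ventilation, acid–base and CO2 elimination variables are to be "measured before insufflation, during surgery and after deflation of the pneumoperitoneum", which again supplies a baseline.

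Under Study design and randomization, "patients will be randomly stratified regarding type of operation in a 1:1 ratio". The Statistical considerations section repeats that "Stratification according to the type of surgery was done".

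The Statistical methods section then gives one rule for metric variables. "Metric variables data sets will be checked for normal distribution" by a Lilliefors-corrected Kolmogorov–Smirnov test at 5%. "Normally distributed data sets will be compared between the groups by the" t-test for independent samples, with a Levene-based correction for unequal variances. "If there is a significant deviation from the normal distribution the exact" Mann–Whitney test replaces it. No covariate, stratum or repeated-measures model is named, and the resulting P values are described as descriptive.

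**The concern.** The design collects two things that would sharpen these comparisons, a baseline value per patient and a balanced stratification factor, and the stated test uses neither explicitly. The section names the test outright, so this is a choice made in the article rather than a detail left open.

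The article itself gives reason to think that operation type matters here. The Statistical methods section says that colorectal operations clearly differ in duration from the other two types. The Discussion ties the severity of the physiological disturbance to exposure time. Together these imply that operation type is prognostic for the biomarkers and the respiratory variables.

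In addition, the pre-test is applied to each data set separately. The same biomarker may be compared by means at one sampling time and by ranks at the next, for no scientific reason. At stake are the width of the intervals and the readability of the secondary results over time.

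**Working it through.** **Inputs from the article.** The sample size, 91 per group with 5% dropout, is based on operation time. No power or sample size is given for the biomarker or ventilation endpoints, so there is no figure of the plan to reproduce on this point. Evaluable patients: 91 × 0.95 = 86.45, taken as 86 per arm.

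**Inputs assumed.** The article gives neither the correlation ρ between baseline and post-value nor the share R² of variance explained by operation type. Ranges are used.

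**Step 1: baseline.** Take the variance of the unadjusted post-value comparison as 1.
- Change score, equal variances before and after: 2(1 − ρ).
- ANCOVA on baseline: 1 − ρ².
- ANCOVA relative to change score: (1 − ρ²) / [2(1 − ρ)] = (1 + ρ)/2.

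| ρ (assumed) | Change score | ANCOVA | ANCOVA / change score | Per-arm size at which post-values match ANCOVA with 86 |
|---|---|---|---|---|
| 0.3 | 1.40 | 0.91 | 0.65 | 86/0.91 ≈ 95 |
| 0.5 | 1.00 | 0.75 | 0.75 | 86/0.75 ≈ 115 |
| 0.7 | 0.60 | 0.51 | 0.85 | 86/0.51 ≈ 169 |

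For an effect that the post-value test detects with 80% power at 86 per arm, ANCOVA gives 83.6%, 89.9% and 97.5% at the three correlations. Change scores give 65.8%, 80.0% and 95.1%. Below ρ = 0.5 the change score is less precise than the raw post-value.

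**Step 2: stratum.** If stratified randomisation balances the arms within operation type, the true variance of the arm difference contains only the within-type part, 1 − R². The unstratified test uses the total variance. Its standard error is therefore too large by 1/√(1 − R²): 1.05, 1.20 and 1.41 at R² = 0.1, 0.3 and 0.5.

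**Step 3: simulation of the whole rule.** Assumptions: 86 per arm, operation mix 34/26/26, effect 0.4 within-type SD, ρ = 0.5, normal data within type, normality tested in each arm, 1,500 runs, and the post-values of one operation type shifted by 0, 1 or 2 SD.

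| Shift | Planned rule, post-values | Planned rule, change scores | ANCOVA, baseline + type |
|---|---|---|---|
| 0 SD | 0.74 | 0.74 | 0.84 |
| 1 SD | 0.67 | 0.67 | 0.85 |
| 2 SD | 0.48 | 0.47 | 0.87 |

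With no effect and a 2 SD shift, the planned rule on post-values rejected in about 1% of runs (nominal 5%), against about 5% for ANCOVA. Step 2 predicts this. With 26 of 86 patients shifted by 2 SD, the between-type variance is 4 × 0.302 × 0.698 = 0.84, so R² = 0.84/1.84 ≈ 0.46. The standard error is then 1/√0.54 ≈ 1.36 times too large, and the effective critical value is 1.96 × 1.36 ≈ 2.67, a two-sided level of about 0.8%.

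**Step 4: switching.** In a further simulation of the same kind (1,000 runs), the pre-test moved to Mann–Whitney in about 7–8% of data sets at shifts of 0 and 1 SD, and in about 25–28% at 2 SD. The choice can thus differ between sampling times of one variable, most readily when operation type has a large effect.

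**The case against.** - **Change scores.** A reader might infer that baseline is ignored throughout. The documents do not support that for the cytokines: the endpoint is worded as changes, and a change is itself a metric variable to which the rule can be applied. This stands. But no formula is given, the wording does not cover the ventilation values, and change scores are still less precise than ANCOVA at every ρ below 1 and still omit operation type.
- **Bias.** A reader might infer that the results are biased or invalid. They are not. Under randomisation, omitting covariates costs precision, and an ignored balanced stratum makes the test conservative. The endpoints are secondary and descriptive, and no sample size or confirmatory claim depends on them.
- **Switching.** A reader might infer that the test could differ between arms, or that no common summary would exist. Each arm comparison uses one test, so only time points or variables can differ. The section on presentation of results fixes the same descriptive statistics for all metric variables whichever test is used, and confidence intervals are planned for selected variables.
- **Size.** The gain cannot be read from the documents. At ρ = 0.3 with little effect of operation type it is small. The change-score ratios need equal variances, the Step 1 formulas do not describe the Mann–Whitney branch, and the 1% error rate needs an assumed 2 SD shift.
- **Model fit.** Operative procedure places ventilation under a strict protocol, and Background says that hypercapnia is usually avoided by ventilatory changes. A normal model with baseline is not clearly suited to a setting such as PEEP. Table 2 lists blood gases only at incision/insufflation and at suture/deflation, so a true pre-insufflation acid–base value is uncertain. Both points stand and limit the fix.

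**Conclusion.** The point holds as a matter of precision. The stated rule leaves out the randomisation stratum and does not say that baseline is used, although both are part of the design. ANCOVA on baseline would reduce variance by 9%, 25% or 49% relative to post-values, and by 35%, 25% or 15% relative to change scores, at assumed correlations of 0.3, 0.5 and 0.7. The change-score figures also assume equal variances. Adjusting for operation type adds to this to the extent that it is prognostic, which the article implies but does not quantify. A gain equivalent to a third more patients (1/0.75) is the middle of an assumed range, not an established figure. The primary endpoints and their conclusion are unaffected. The change is worth making because it improves the estimates without new patients.

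**What to change.** For the six biomarkers (log scale) and the continuous respiratory and acid–base outcomes, replace the pre-test rule by one prespecified ANCOVA or repeated-measures model. Include the pre-operative or pre-insufflation value, operation type, arm, time and arm-by-time. Report ratios of geometric means for the biomarkers and mean differences for the others, with 95% confidence intervals at each time.

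For variables largely set by the anaesthetist, such as PEEP, or without a true pre-insufflation value, name in advance a Welch test or a rank test stratified by operation type. Reconcile the Secondary endpoints section with Table 2 on when blood gases are taken, so that it is clear which acid–base values can serve as baseline.

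The cost is revised wording and routine programming. No additional patients or procedures are needed. The cytokines are to be assayed together at the end of recruitment, so the model should be fixed before those results are seen.
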